### Participant timeline {13}

The participant timeline is presented in Table 1.

**Table 1 Tab1:** Schedule of enrollment, assessments, and data collection for the period of the trial

	Study period							
Time points	Enrolment	Allocation	Post allocation (months)					
	-t_0_	t_0_	6	12	18	24	30	36
**Enrolment**								
Eligibility screen	X							
Informed consent	X							
Allocation		X						
**Assessments**								
**Conventional screening**								
Semi-annual ultrasound and alpha-fetoprotein for all people with cirrhosis hepatitis B virus infection with any degree of fibrosis				X		X		X
Digital rectal examination and anal cytology to all MSM every 1–3 years				X		X		X
Cervical cytology every 1–3 years to all sexually active women, at least 25 to 64 years old				X		X		X
Mammogram every 1–3 years to women between 50 and 70 years				X		X		X
Rectal digital exam ± PSA every 1–3 years for all men> 50 years				X		X		X
Fecal occult blood test every 1–3 years in people between 50 and 75 years				X		X		X

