### Intervention description {11a}

Conventional group:

a. Semi-annual ultrasound and alpha-fetoprotein for all patients with cirrhosis and those with HBV infection with any degree of fibrosis.

b. Digital rectal examination and anal cytology every 1–3 years for all MSM men and anoscopy in case of cytology abnormal.

c. Cervical cytology every 1–3 years to all sexually active women, at least in those between 25 and 64 years.

d. Mammogram every 1–3 years to women between 50 and 70 years.

e. Rectal digital exam ± prostate-specific antigen (PSA) every 1–3 years for all men> 50 years.

f. Fecal occult blood test every 1–3 years in people between 50 and 75 years.

Enhanced group:

a. Annual LDCT to patients over 40 years of age, active smokers or who have quit in the last 3 years, with an accumulated index ≥ 20 pack-years and without contraindications for thoracic surgery, and without lung infections in the last 2 months.

b. Semi-annual ultrasound and alpha-fetoprotein for all people with chronic liver disease with fibrosis ≥ F3 of any cause (including HCV infection) or with any fibrosis for patients with HBV. Serum will be collected from all participants to be able to subsequently perform additional determinations such as alpha-fetoprotein-L3, decarboxyproprombin, or alpha-L-fucosidase.

c. Semi-annual digital examination and anal cytology to all MSM men and anoscopy in case of abnormal cytology.

d. Semiannual cervical cytology to all sexually active women between the ages of 21 and 64, including cotest (cervical cytology and HPV test) from the age of 30 if available (when cotest is available, controls will be made annually).

e. Annual mammogram for women between 50 and 70 years.

f. Annual PSA and digital rectal exam to all men ≥ 50 years.

g. Annual fecal occult blood to people> 40 years.

h. Annual general inspection for skin lesions suggestive of malignancy.

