**Enhanced screening**								
Over 40 years of age, active smokers or who would have abandoned in the last 3 years, with an accumulated index ≥ 20 pack-years and without contraindications for thoracic surgery, and without recent lung infections in the last 2 months				X		X		X
Semi-annual ultrasound and alpha-fetoprotein for all people with chronic liver disease with fibrosis ≥ F3 of any cause (including HCV infection) or any fibrosis for hepatitis B virus			X	X	X	X	X	X
Digital examination and semi-annual anal cytology MSM			X	X	X	X	X	X
Semiannual cervical cytology to all sexually active women between the ages of 21 and 64, including cotest (cervical cytology and HPV test) from the age of 30 if available (in that case, controls will be made annually)			X	X	X	X	X	X
Annual mammogram for women between 50 and 70 years				X		X		X
PSA and annual digital rectal exam to all men ≥ 50 years				X		X		X
Annual fecal occult blood to people > 40 years				X		X		X
Annual general inspection for skin lesions suggestive of malignancy				X		X		X

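### Table 1 marks the control arm's semi-annual liver surveillance only once a year, against its own row label and the intervention description

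*Protocol article*

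**What the plan says.** Intervention description {11a}, item a of the conventional group, specifies "Semi-annual ultrasound and alpha-fetoprotein for all patients with cirrhosis and those with HBV infection with any degree of fibrosis". In Table 1 (Participant timeline {13}) the matching control row is labelled "Semi-annual ultrasound and alpha-fetoprotein for all people with cirrhosis hepatitis B virus infection with any degree of fibrosis" and carries marks at months 12, 24 and 36.

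The enhanced half of Table 1 has a row beginning "Semi-annual ultrasound and alpha-fetoprotein for all people with chronic liver disease with fibrosis ≥ F3 of any cause". It is marked at months 6, 12, 18, 24, 30 and 36.

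The other five control rows repeat the 1–3-year range from {11a}, for example "Mammogram every 1–3 years to women between 50 and 70 years", "Digital rectal examination and anal cytology to all MSM every 1–3 years" and "Cervical cytology every 1–3 years to all sexually active women, at least 25 to 64 years old". Each is marked at months 12, 24 and 36. The enhanced mammogram row, "Annual mammogram for women between 50 and 70 years", has those same three marks.

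**The concern.** A schedule table is what a centre uses to book tests, and this one is titled as covering assessments and data collection. For control-arm liver surveillance its label and its marks disagree, and the marks also disagree with {11a}. A centre working from the marks and a centre working from the text would plan different control schedules. Under {18b} the CRO checks adherence to the protocol, but three examinations in 36 months match the marks and fall short of the text, so monitors have no single standard to check against.

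The comparator is also affected. In {11a} the liver interval is the same in both arms and only eligibility differs: cirrhosis against fibrosis of F3 or more, with any fibrosis in HBV in both arms. The marks add a difference in frequency. Liver is one of the named sites of the primary outcome in Outcomes {12}, and the number of control tests also enters the cost-utility comparison.

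The rows set at every 1–3 years raise a smaller question: whether three marks mean three required tests, or three visits at which a test may fall.

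**Working it through.** No sample size or power figure is involved. The check compares the number of marks in each row with the number that its stated interval implies over 36 months.

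**Inputs.** The intervals come from {11a} and the Table 1 row labels. The marks come from Table 1, whose post-allocation columns are months 6, 12, 18, 24, 30 and 36.

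**Formula.** Implied number = 36 months / interval in months. Semi-annual gives 36/6 = 6. Every 1–3 years gives between 36/36 = 1 and 36/12 = 3.

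| Test | Control interval | Implied, control | Marks, control | Marks, enhanced |
|---|---|---|---|---|
| Liver ultrasound and alpha-fetoprotein | semi-annual | 6 | **3** (12, 24, 36) | 6 |
| Anal examination and cytology | 1–3 years | 1 to 3 | 3 | 6 |
| Cervical cytology | 1–3 years | 1 to 3 | 3 | 6 |
| Mammogram | 1–3 years | 1 to 3 | 3 | 3 |
| Rectal examination ± PSA | 1–3 years | 1 to 3 | 3 | 3 |
| Faecal occult blood | 1–3 years | 1 to 3 | 3 | 3 |

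**Liver row.** The shortfall is 6 − 3 = 3 marks, at months 6, 18 and 30. A fault in reading the table is unlikely. The marks line up with the header columns, and the same table shows month 6, 18 and 30 marks in three enhanced rows (liver, anal and cervical).

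**1–3-year rows.** Three marks lie inside the allowed 1 to 3, at its upper end, so there is no contradiction. The marked months coincide between arms for three of the five tests and differ for two (3 against 6). Where they coincide, the arms are not always otherwise identical:

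- Mammogram: same ages (50–70), so identical if control follows the marks.
- Prostate: PSA is optional in control and required in enhanced; ages are >50 against ≥50.
- Faecal occult blood: ages 50–75 against >40.

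**The case against.** Two of the three statements of the control liver interval, {11a} and the row label, agree, and only the marks differ. A careful centre would notice the label. The control arm is described as standard of care, and {11d} permits any concomitant intervention needed for medical care. The Discussion already recognises that screening differs between centres and plans to unify the control protocol from baseline survey data.

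Much of this stands, and it limits what may be inferred. A reader might go further in four ways that the document does not support:

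- **That control patients with cirrhosis or HBV will lose half their liver examinations.** The label and {11a} both say semi-annual, and usual care continues. The document shows conflicting instructions, not tests forgone.
- **That the 1–3-year rows also contradict {11a}.** Yearly testing complies with both, and the labels repeat the range.
- **That Table 1 removes the contrast for breast, prostate and colorectal cancer.** The latitude in {11a} itself already allows yearly control testing. Prostate and faecal occult blood also keep the differences in content or age shown above, and the marks for anal and cervical cytology differ between arms.
- **That the primary result is biased in a known direction.** The protocol gives neither the number of control patients eligible for liver surveillance nor the expected number of liver cancers.

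None of this removes the mismatch in the liver row. The plan in the Discussion concerns variation in practice between centres and does not say which of two conflicting instructions in the protocol applies.

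**Conclusion.** The plan is wrong as written on the control-arm liver row: 3 marks against the 6 implied by its own label and by {11a}, and against 6 in the enhanced row with the same interval. For patients who would qualify in either arm (HBV with any fibrosis, and cirrhosis if it is taken to fall within fibrosis of F3 or more), the marks imply a difference in frequency that {11a} does not contain. The conclusion assumes only that the marks sit under the months shown in the header.

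The 1–3-year rows are a secondary matter of clarity. The table shows the most frequent schedule in the range and does not say whether its marks are binding.

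The consequence is two control standards across 30 centres, for a named primary-outcome site. Its numerical effect on the primary comparison is unknown.

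**What to change.** In one amendment, reconcile the conventional and enhanced items of {11a} with the conventional and enhanced parts of Table 1, so that the text, the row label and the marks state one control-arm liver schedule. The sponsor and clinical leads must decide which interval applies; this review does not choose one.

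In the same amendment, add a note to Table 1 saying whether the marks on the 1–3-year rows are fixed visits or visits at which the test may be done. Send the single reconciled control schedule to all centres and to the CRO, so that monitoring uses the same standard.

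The cost is a short amendment and a notice to centres. No sample size figure or planned analysis changes.

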**Enhanced screening**								
Over 40 years of age, active smokers or who would have abandoned in the last 3 years, with an accumulated index ≥ 20 pack-years and without contraindications for thoracic surgery, and without recent lung infections in the last 2 months				X		X		X
Semi-annual ultrasound and alpha-fetoprotein for all people with chronic liver disease with fibrosis ≥ F3 of any cause (including HCV infection) or any fibrosis for hepatitis B virus			X	X	X	X	X	X
Digital examination and semi-annual anal cytology MSM			X	X	X	X	X	X
Semiannual cervical cytology to all sexually active women between the ages of 21 and 64, including cotest (cervical cytology and HPV test) from the age of 30 if available (in that case, controls will be made annually)			X	X	X	X	X	X
Annual mammogram for women between 50 and 70 years				X		X		X
PSA and annual digital rectal exam to all men ≥ 50 years				X		X		X
Annual fecal occult blood to people > 40 years				X		X		X
Annual general inspection for skin lesions suggestive of malignancy				X		X		X

### Sample size {14}

The incidence of NADCs in the previous studies SMART and ESPRIT in virologically suppressed patients with CD4> 350 and over 40 years old was approximately 0.04% during 5 years of follow-up [27]. An Italian study described an incidence of NADCs of 0.67 per 100 person-years of follow-up [28]. In the CoRIS cohort, with 31.228 person-years of follow-up, a total of 136 NADCs were diagnosed, and the incidence was 0.43 per 100 person-years of follow-up. In a study of lung cancer screening among smokers, the prevalence of lung cancer was 2.03% [29]. For the calculation of the sample size, we have estimated an incidence of cancer diagnosed at an early stage of 2% in in the intervention group and 1% in the control group. With a statistical power of 80% and a loss to follow-up percentage of 20%, it is estimated that for a unilateral contrast it would be necessary to include 2.319 subjects in the exposed group (enhanced intervention) and 2.319 in the unexposed group (standard intervention) (1:1), with a total sample of 4.638 patients.

### Recruitment {15}

This protocol corresponds to an independent clinical study carried out in the framework of the cohort of the Spanish AIDS research network. The main strategy to achieve an adequate number of patients to reach the calculate sample size is to disseminate the project among the centers participating in the cohort.

## Assignment of interventions: allocation

### Sequence generation {16a}

The study will be operated by an electronic data collection notebook (REDCap®). This software allows assigning random numbers to the recruited patients. Also, there is a plan restriction to ensure well-balanced proportions of patients and representation of genders per branch and center. Specifically, random allocation will be carried out in blocks of twenty patients with a 1:1 ratio to either intervention group in men and women .

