### Eligibility criteria {10}

Inclusion and exclusion criteria for participants:

Inclusion criteria: adult patients ≥ 18 years with confirmed HIV infection and who agree to participate in the study and sign the informed consent.

Exclusion criteria: any active AIDS-defining disease, current or past NADC, life expectancy < 5 years, pregnancy or lactation, patients who refuse to participate in the study, any other criteria that in the judgment of the clinician should prevent the patient to participate in the study.

Eligibility criteria for study centers: Spanish hospitals with HIV/AIDS Unit and Infectious Diseases/HIV (ID/HIV) specialists.

Eligibility criteria for study individuals who will perform the interventions: ID/HIV specialists, radiologists, gynecologists, and surgeons.

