### Who will take informed consent? {26a}

Participants meeting the study criteria will be invited by their doctors in charge to join the study during their routine medical visits, regardless of time from HIV diagnosis and the standard screening procedures being carried out in their centers, explaining the possible benefits and risks of the trial, and they will obtain the informed consent to participate in the study.

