### Implementation {16c}

The enrolment of the patients will be done by the involved physicians in the study. Each participant center has a research team to carry out the rest of the activities of the project and a central Contract Research Organization (CRO) gives support for all of them.

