## Assignment of interventions: blinding

### Who will be blinded {17a}

This is an open label trial.

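### A single, published block size of twenty in an open-label trial lets a recruiting doctor count to the end of a block, if the blocks run within centre, and so know up to about 7–9% of assignments in advance

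*Protocol article*

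**What the plan says.** Under Sequence generation {16a}, the protocol article gives one block size: "random allocation will be carried out in blocks of twenty patients with a 1:1 ratio to either intervention group in men and women". The sentence before it states the aim, a "plan restriction to ensure well-balanced proportions of patients and representation of genders per branch and center". Sex is therefore an explicit blocking factor. Centre appears only in the balance aim.

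Under Who will be blinded {17a}: "This is an open label trial". Past assignments are thus visible at the centre.

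The people who recruit are the people who treat. Patients "will be invited by their doctors in charge to join the study during their routine medical visits" (Who will take informed consent? {26a}), and "The enrolment of the patients will be done by the involved physicians in the study" (Implementation {16c}). The exclusion criteria include "any other criteria that in the judgment of the clinician should prevent the patient to participate in the study" (Eligibility criteria {10}).

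The Concealment mechanism {16b} section says that REDCap implements the sequence and that investigators have a guidance datasheet. Neither that section nor Implementation {16c} varies the block size or says that it is withheld from recruiters. Under Intervention description {11a}, low-dose CT and skin inspection are listed only for the enhanced group.

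**The concern.** REDCap hides the list but cannot hide the end of a block that can be counted. Once one arm has received ten patients in a block of twenty, every remaining assignment in that block is certain. A doctor who knows that the next patient will go to the enhanced arm can choose whom to bring forward or hold back. Several markers of cancer risk, such as smoking, age and liver disease, are plain at a routine visit, and CT screening is offered in only one arm.

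If steering happened, its natural direction would put higher-risk patients in the enhanced arm. That would add early cancers there, in the direction of the superiority hypothesis. The expected event counts are small (1% and 2% under Sample size {14}), so even a modest shift in case mix matters. Analysing all patients as randomised does not help, because the groups would already differ on entry.

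**Working it through.** **Inputs.** Block size 20 at 1:1, so m = 10 per arm (Sequence generation {16a}); 30 centres (Study setting {9}); 4,638 patients, 2,319 per arm, 20% loss and 1% early cancer in the control group (Sample size {14}). The protocol gives no figure for predictability, so there is none to reproduce.

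**Certain assignments in a complete block.** Assignment k is certain if one arm is already full after k − 1 patients. The probability is 2·C(k−1, 10)/C(20, 10).
- Positions 1 to 10: never certain.
- Position 17: 9%; 18: 21%; 19: 47%; 20: always.
- Sum over the block: 2m/(m+1) = 20/11 = 1.82, a share of 1/11 = 9.1%.
- A simulation of 200,000 blocks gives 9.09%.
- Ceiling over the trial: 4,638/11 ≈ 422 assignments, about half of them (1 in 22 of all assignments) to the enhanced arm.

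**Incomplete last blocks.** If blocks run by centre and sex, the average stratum holds 4,638/(30 × 2) = 77.3 patients. A stratum of 77 has three complete blocks and 17 patients of a fourth, which gives 5.59/77 = 7.3% certain. Assuming 15% to 50% women and even or uneven centre sizes, the share is 7.3% to 8.3%. Hence about 7–9%.

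**Overall guessing.** A recruiter who always guesses the arm that is behind is right in [m + (4^m/C(2m, m) − 1)/2]/(2m) = 61.7% of complete blocks' assignments, against 50% by chance.

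**Illustration of the effect on the error rate.** Take no true effect, 1% early cancer in both arms, and 2,319 × 0.8 ≈ 1,855 evaluable per arm.
- SE = √(2 × 0.01 × 0.99/1,855) = 0.327 percentage points.
- Assumption: patients placed in known enhanced slots have a risk 1 point higher than those placed in known conventional slots.
- False difference = certain share × 1 point. One-sided error = P(Z > 1.645 − false difference/SE).

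| Certain share | Centres steering | False difference (points) | One-sided error |
|---|---|---|---|
| 9.1% | all | 0.091 | 8.6% |
| 8% | all | 0.080 | 8.1% |
| 9.1% | a quarter | 0.023 | 5.8% |
| 8% | a quarter | 0.020 | 5.7% |

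**Alternative schemes.** These are simulated for strata of 77, with an observer who sees all earlier assignments and knows the list of possible sizes.

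| Block sizes | Certain | Guessed correctly |
|---|---|---|
| Fixed 20 | 7.3% | 61% |
| Random 16, 20, 24, 28 | about 0.5% | about 60% |
| Random 4, 6, 8 | about 2.3% | about 68% |

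**The case against.** The main objection concerns the premise. The sentence that defines the blocks names only men and women. If the blocks run by sex across all 30 centres, a local doctor sees a small part of each block and can hardly predict anything. This stands: within-centre blocking is inferred from the balance aim, so the finding is conditional on it. But if the blocks do span centres, they do not secure the per-centre balance that the same section announces, so the text needs clarifying either way.

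The opportunity is also narrow. It needs a recruiter who follows every assignment in the stratum, although several physicians may recruit. With about 77 patients per stratum over roughly 42 months (June 2019 to December 2022, Trial status), a block takes about 11 months on average (20/77.3 × 42) and yields about 0.9 known enhanced slots. Concomitant care needed for medical reasons is allowed in both arms (Relevant concomitant care {11d}), so a worried doctor can investigate a patient without influencing allocation. These points limit the likely size but do not remove the weakness.

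Twenty is in itself a large block. A known fixed block of 4 would make 1 in 3 assignments certain. The weakness is that there is one disclosed size in an unblinded trial, not the number twenty.

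A reader might infer a much larger effect, with an error of about 14%. That needs every centre to steer every known slot with a 2-point gap in risk (0.091 × 2 = 0.18 points). The only nearby figure in Sample size {14}, 2.03%, is a prevalence of lung cancer in a screening study of smokers. It is not a difference in risk of early cancer. Set against the assumed 1% base it suggests a gap of about 1 point. A reader might also infer that steering has occurred. Nothing in the document shows that.

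**Conclusion.** The point holds as a conditional and modest weakness that is cheap to repair. The document fixes and publishes a single block size in an open-label trial in which treating doctors control invitation and timing, and it states no safeguard against counting. If the blocks run within centre, up to about 7–9% of assignments could be known in advance, about half of them to the enhanced arm. That share is exact for complete blocks and rests on assumed stratum sizes for incomplete ones.

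The error of about 8–9% with all centres steering, or about 5.7% with a quarter, is an illustration. It rests on an assumed 1-point risk gap and on every known slot being used at the centres concerned. It is not an estimate of what has happened.

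**What to change.** 1. State in Sequence generation {16a} whether the blocks run within centre by sex, or by sex across centres.
2. If they run within centre, have a new list loaded into REDCap for all unused assignments, with block sizes drawn at random from fairly large values (for example 16, 20, 24 and 28). Keep the sizes out of every document that centres see. Avoid small random blocks, which are guessed more often. The gain is in certainty only: certain assignments fall to about 0.5%, while overall guessing stays near 60%.
3. For patients already enrolled under fixed blocks, compare baseline risk (age, pack-years, eligibility for low-dose CT) by arm among the assignments that were certain given the earlier ones in their block. Blocks already used cannot be changed, so this check is the only protection for them.
4. Stratifying the primary comparison by the randomisation factors is a harmless addition, but it does not cure selection before randomisation.

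The cost is one replacement allocation table, a wording amendment and one baseline table, with no extra patients. The largest possible within-stratum imbalance rises from 10 to 14, which is slight at about 155 patients per centre (4,638/30).
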